### Participants

This study is an RCT (NCT04068805) with an initial target sample size of 400 participants (200 participants per condition). Recruitment will continue until 400 participants have successfully completed pretesting and have been randomized to condition.

Although previous RCTs using Happify Health had response rates ranging from 56% to 72% for an 8-week posttest [60], as the first attempt to include long-term follow-up of Happify Health users, the level of attrition beyond the 8-week intervention is difficult to estimate. The few previous tests of mental health interventions on people with diabetes that included long-term follow-up reported relatively low attrition for 6-month [35,64] and 12-month [34,65] follow-ups; however, all these studies involved in-person interventions and often included booster sessions, thereby increasing the level of contact with participants and increasing response rates. The levels of attrition are much higher in research using digital interventions [66], although dropout rates are lower in RCTs than in open-access interventions [67]. Consequently, although we predict attrition for long-term follow-ups to be higher in this study than in previous research with in-person interventions, it is unclear what percentage of participants to expect for our 3-, 6-, and 12-month assessments.

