### Outcome Measures

All assessments will be administered via Happify Health, and participants who do not complete measures will be sent email reminders; however, participants may withdraw from the study or skip assessments at any time. To link participant data across assessments and other data collections, each participant will be assigned a unique study ID number; participants will otherwise remain anonymous throughout the study. In addition to the primary and secondary outcome measures described in the following sections, other exploratory measures will also be included that are not reported here.

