### Procedures

Participation in this study will take place over approximately 14 months, including an 8-week intervention (or corresponding control) delivered via Happify Health as well as follow-up assessments at 3, 6, and 12 months postintervention. To ensure that HbA_1c_ levels reported postintervention reflect average glucose levels only after starting the intervention, all participants will begin the study within 3 weeks of obtaining their most recent HbA_1c_ levels. Participants who indicate that their most recent HbA_1c_ levels were obtained before that when contacted by phone will wait to begin the study until they obtain their following HbA_1c_ measurement and researchers confirm that they meet the inclusion criterion.

Once participants are ready to begin the study, they will be directed to complete 1 week of daily assessments without exposure to either condition. Participants who complete fewer than 5 of these assessments will be disqualified from the study. Those who complete at least five of the daily assessments during this qualifying period will be directed to download the mobile app and complete the regular onboarding questionnaire for Happify Health; participants will be randomly assigned to either the positive emotion regulation skills intervention group or the control group upon completing these questions. Following randomization, participants will be prompted to complete the baseline assessment.

Participants will then be instructed to begin using their assigned version of Happify Health. Although participants will not be given explicit instructions on how often they should use the platform, they will be encouraged to engage with the platform daily. Participants will receive daily push notifications on their mobile device to remind them to access the platform and answer daily questionnaires, and they will also receive weekly emails as part of the Happify Health platform to help keep them engaged with the program. In addition, to improve use rates and participant retention, research staff will call participants to inquire about problems when a participant has not engaged with the Happify Health platform at all for 1 week.

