After 8 weeks, participants will be instructed to complete the postintervention assessment; this assessment will be identical to the baseline with the exception of HbA_1c_ assessment, which will occur 3 weeks later via the Happify Health app. After completing this assessment, participants will receive an email instructing them to answer daily questions for 1 week and to remind them that we will contact them again in 3, 6, and 12 months for follow-up assessments and that they should continue to use their assigned version of Happify Health as they see fit. Participants will then receive emails instructing them to complete each of the 3-, 6-, and 12-month assessments, which will also be accompanied by 1 week of daily assessments at each follow-up period. Table 1 provides the schedule of activities. To improve participant retention, participants who do not complete the postintervention, 3-, 6-, and 12-month assessments will also receive a reminder phone call from the research staff.

**Table 1 table1:** Schedule of activities for prescreen, intervention period, and follow-up assessments.

Assessments		Time										
		Prescreen	Week 1: qualifying period	Week 2: baseline and first week of intervention	Weeks 3-9: intervention	Week 10	Week 12	Week 21: 3-month follow-up	Week 24	Week 33: 6-month follow-up	Week 36	Week 57: 12-month follow-up

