### Analysis Plan

We plan to analyze the changes in primary and secondary outcomes across the 2 conditions using hierarchical linear modeling (HLM). We will compute the change trajectories on each outcome over the course of the study assessments (ie, at baseline, immediately postintervention, and at 3-, 6-, and 12-month follow-ups). These trajectories will then be averaged together within each condition, so we can compare the trajectories for each outcome across the 2 conditions to determine if there was greater improvement in the positive emotion regulation skills intervention group relative to the control group.

We plan to use participants’ daily assessments in 2 ways. First, we will compute growth trajectories for each participant using their daily assessments to explore when people tend to experience improvements in diabetes-related distress, diabetes regimen adherence, and mood during the intervention. Second, as retrospective reports can sometimes lead to inflated or inaccurate information compared with daily assessments [75], we will use daily assessments to compute weekly averages for diabetes-related distress, diabetes regimen adherence, and mood during and after the intervention. These weekly averages will then be used as outcome variables in the same HLM analyses described earlier.

Previous research on the impact of health care interventions on people with poorly managed diabetes suggests that effects may be most effective among people with especially poor glycemic control or HbA_1c_ levels above 9.5% [76]. Consequently, we plan to examine the effects of baseline HbA_1c_ as a moderator of the effects of the intervention on changes in the primary and secondary outcomes. Similarly, we also plan to examine the effects of baseline depressive symptoms as a moderator of the effects of the intervention. Finally, given that the effects of Happify Health use are typically moderated by usage [57-61], we plan to examine the effects of frequency of usage as another moderator of changes in the primary and secondary outcomes.

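### The baseline assessment is prompted only after randomisation, so four self-report scales have no value from before allocation

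*Protocol article*

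**What the plan says.** The Procedures section of the protocol article gives the order step by step. After a qualifying week of daily items, those who pass "will be directed to download the mobile app and complete the regular onboarding questionnaire for Happify Health". Then "participants will be randomly assigned to either the positive emotion regulation skills intervention group or the control group upon completing these questions". The next sentence is "Following randomization, participants will be prompted to complete the baseline assessment". After that, "Participants will then be instructed to begin using their assigned version of Happify Health".

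Table 1 places the baseline in a column labelled "Week 2: baseline and first week of intervention". Outcome Measures states that "All assessments will be administered via Happify Health", that missed measures trigger email reminders, and that participants may skip any assessment. Participant Compensation pays for each main assessment except the baseline.

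The Participants section describes the recruitment target differently: "Recruitment will continue until 400 participants have successfully completed pretesting and have been randomized to condition".

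The Analysis Plan makes the baseline the first point of each outcome's trajectory. It also uses baseline HbA1c as a moderator, and for depression says that "we also plan to examine the effects of baseline depressive symptoms as a moderator of the effects of the intervention".

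**The concern.** A baseline is useful in a randomised comparison because allocation cannot have affected it. Once it is collected after allocation, that is no longer guaranteed by design.

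Two things can go wrong. First, answers may shift. The two versions look different: one features a track whose description directs attention to how negative emotions affect diabetes, while the other offers polls followed by psychoeducational text. Someone who has seen either could rate diabetes distress or positive affect differently. Second, completion may differ by arm, because a person who is disappointed with the assigned version can skip the assessment.

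Either would carry into the estimated change on the scale concerned, and for a scale with no earlier value the analysis could not recover what was lost.

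**Working it through.** **Order of events.** The Procedures sequence is: qualifying week, download, onboarding questions, randomisation, baseline prompt, instruction to start using the assigned version. No section of the article places the baseline assessment before randomisation, and none makes its completion a condition for opening arm content.

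**Which measures have an earlier value (Table 1, with Recruitment Strategy and Procedures).**

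| Measure | Before randomisation | Week 2 baseline |
|---|---|---|
| HbA1c | Prescreen; reading obtained within 3 weeks before study start | Reported again |
| PHQ | Prescreen | Measured again |
| Daily distress, adherence, mood | Week 1, at least 5 of 7 days | Continue |
| Diabetes distress scale | None | First measurement |
| Medication adherence scale | None | First measurement |
| Self-care activities | None | First measurement |
| Positive affect subscale | None | First measurement |

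The exposure therefore falls on four of the five secondary questionnaires.

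**Support for completion.** The baseline is unpaid, against US $15 for each later main assessment. Email reminders apply to any missed measure. Reminder calls are listed for the postintervention, 3-, 6- and 12-month assessments, but not for the baseline. A separate call is made after a week with no platform engagement at all. It might catch some missed baselines, but its stated purpose is platform use.

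**Illustration of size.** The article has no figure to reproduce beyond 2 × 200 = 400. Assume no true effect, a baseline shift of *s* SD in one arm only, correlation ρ between baseline and follow-up, *n* per arm and two-sided α = 0.05. Both *s* and ρ are assumptions.

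- Change score: bias = *s*; SE = √(2(1−ρ)) × √(2/*n*).
- Baseline-adjusted: bias = ρ*s*; SE = √(1−ρ²) × √(2/*n*).
- False-positive rate = Φ(bias/SE − 1.96) + Φ(−bias/SE − 1.96).

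Worked case: *n* = 200, *s* = 0.1, ρ = 0.5. The change-score SE is √1 × √0.01 = 0.100, so bias/SE = 1.00 and the rate is Φ(−0.96) + Φ(−2.96) = 0.17. For the adjusted analysis, bias = 0.05, SE = √0.75 × 0.1 = 0.087, and the rate is 0.089.

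| *n* per arm | *s* | ρ | Change | Adjusted |
|---|---|---|---|---|
| 200 | 0.1 | 0.5 | 17% | 9% |
| 200 | 0.1 | 0.7 | 25% | 17% |
| 200 | 0.2 | 0.5 | 52% | 21% |
| 200 | 0.2 | 0.7 | 73% | 50% |
| 112 | 0.1 | 0.5 | 12% | 7% |
| 112 | 0.1 | 0.7 | 16% | 11% |

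The 112 is 200 × 0.56, the lower end of the 8-week response range in the Participants section. These formulas use one baseline and one follow-up. The planned hierarchical model uses five assessments and would weight the baseline according to how time is modelled, so the rates show an order of magnitude and are not predictions.

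**The case against.** Much can be said for the plan, and most of it stands.

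**The primary outcome is largely protected.** A reader might infer that baseline HbA1c is compromised. The documents do not support that. The test precedes study start, the value is given in the screening survey and asked again by phone, and app use cannot alter a test already taken. Only the Week 2 re-report follows allocation.

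**The moderators have earlier values.** HbA1c and the PHQ are both eligibility criteria and so exist before randomisation. The remaining gap is that the article does not say whether the screening value or the Week 2 value is the baseline for analysis.

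**Exposure before baseline is not stated.** A reader might infer that participants use their assigned version first. Procedures puts the instruction to begin after the baseline prompt, and a weekly column in Table 1 cannot show the order within that week. Nor does the article say that participants are told their arm, and the control is a sham under the same brand. The text is silent on whether content is locked, so this is a risk and not a demonstrated fault.

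**Recall windows help.** The four scales look back over a week or a month, so a prompt answer mostly describes time before allocation. Ratings of how one felt or was bothered can still be coloured by what has just been seen.

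**The Participants sentence is ambiguous.** It might be read as stating the reverse order, or as contradicting Procedures. It joins two conditions with a conjunction and leaves pretesting undefined; the word could mean the qualifying week. It needs clarifying but is not a proven contradiction.

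**Missing baselines are partly handled.** A mixed model can keep people who lack one time point, and email reminders apply. That limits the loss of participants but does not ensure that baseline completion is unrelated to arm.

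**Conclusion.** The point holds for diabetes distress, medication adherence, self-care and positive affect. Their only baseline is prompted after allocation, through the platform, unpaid and skippable, with no stated lock on arm content. Their baselines can be influenced by allocation or be missing differently by arm. The documents do not show that either will happen, and the direction of any bias is unknown.

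HbA1c, the PHQ and the daily items have values from before randomisation, so the primary outcome and the two baseline moderators are much less exposed. For them the remaining issue is which value serves as baseline.

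The illustrated rates, 17% to 25% for change and 9% to 17% with adjustment at 200 per arm, rest on an assumed 0.1 SD shift in one arm and an assumed correlation of 0.5 to 0.7. They show only that a small shift would matter. Because the four scales cannot be measured retrospectively, the order should be settled before recruitment starts.

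**What to change.** Require the full baseline assessment, including the HbA1c value and its date, to be submitted before the randomisation step runs and before any arm-specific content appears. Define pretesting in the Participants section, and reconcile that sentence with Procedures so that it is clear what must be complete for a person to count towards the 400.

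If the order cannot change, name the prescreen HbA1c, the prescreen PHQ and the Week 1 daily values as the baseline and moderator values, and report completion of the Week 2 baseline by arm. This fallback does not help the four scales with no earlier value. It also means using screening values truncated by the entry criteria (HbA1c at least 7%, PHQ at least 15). Regression to the mean would then appear within each arm, but should fall equally on both.

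The main fix costs a change in app flow. A few people will drop out before randomisation instead of after it, which is the better place to lose them.

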### Participant Compensation

Participants will receive three types of compensation throughout the study. After the baseline assessment (for which participants will not be compensated), participants will be compensated with Amazon gift cards valued at US $15 for completing each assessment. As separate compensation for completing daily assessments (as part of the 8-week intervention and during the 3-, 6-, and 12-month follow-ups), participants will earn US $1 for each daily assessment, for a possible total of US $56 for completing daily assessments during the intervention and US $28 for completing the week-long daily assessments at postintervention and during the 3-, 6-, and 12-month follow-ups. Finally, participants will be compensated with US $5 for obtaining and reporting each HbA_1c_ recording after baseline. Thus, participants will be compensated with a total of US $164 if they complete all assessments at all waves of data collection.

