### Primary Outcome: Hemoglobin A_1c_

Participants will self-report their HbA_1c_ levels, a measure of the average blood glucose levels over the past 3 months, 5 times throughout the study: at baseline, week 12 (3 weeks postintervention), week 24 (3 weeks after the 3-month postintervention assessment), week 36 (3 weeks after the 6-month postintervention assessment), and week 57 (at the 12-month postintervention assessment). At each assessment, participants will also report the date when they received this HbA_1c_ reading to verify that it falls in the correct time frame.

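### As written, the phone-reminder rule clearly reaches only one of the four post-baseline HbA1c readings (week 57), leaving the primary outcome at weeks 12, 24 and 36 with e-mail reminders only

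*Protocol article*

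**What the plan says.** Three parts of the protocol article bear on this point.

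- **Reminder calls (Procedures).** The rule lists its triggers: "participants who do not complete the postintervention, 3-, 6-, and 12-month assessments will also receive a reminder phone call from the research staff". In Table 1 these assessments fall at weeks 10, 21, 33 and 57.
- **HbA1c timing.** Procedures describes the postintervention assessment as the same as baseline "with the exception of HbA_1c_ assessment, which will occur 3 weeks later via the Happify Health app". The Primary Outcome section continues the pattern with "week 24 (3 weeks after the 3-month postintervention assessment), week 36 (3 weeks after the 6-month postintervention assessment", and places the last reading at "week 57 (at the 12-month postintervention assessment".
- **Reminders in general (Outcome Measures).** "participants who do not complete measures will be sent email reminders". This covers every measure, including HbA1c.

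Procedures also provides a staff call after a week without any use of the platform. Its trigger is non-use, not a missing HbA1c value.

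**The concern.** The strongest follow-up step in the article, a call from staff about a specific missed assessment, is tied to the questionnaire assessments. Three of the four post-baseline readings of the primary outcome fall on other dates. The exposed participant is one who completes the week-10, 21 or 33 questionnaire, so triggers no call, and then does not send the HbA1c due at week 12, 24 or 36.

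HbA1c is the only glycaemic measure among the listed outcomes, and the participant has to obtain a result as well as report it. Week 12 is the first post-baseline reading, so it is the earliest that could inform the look planned in the Results section, after 20% of the target sample (0.20 × 400 = 80 participants) has completed the intervention. Missing values cost precision, and they can bias the comparison if non-reporters differ systematically from reporters. Both are risks here; the documents do not show that either will occur.

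**Working it through.** **Step 1. Does the article count HbA1c reports apart from the assessments?** The stated total payment offers a check. Inputs from Participant Compensation: US $15 per assessment after baseline, US $1 per daily assessment, and US $5 "for obtaining and reporting each HbA_1c_ recording after baseline".

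- Questionnaire assessments: 4 × 15 = 60
- Daily items during the intervention: 8 weeks × 7 days × 1 = 56
- Daily items in the four follow-up weeks: 4 × 7 × 1 = 28
- HbA1c reports: 4 × 5 = 20
- Total: 60 + 56 + 28 + 20 = 164

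This matches the stated US $164. Without separate HbA1c payments the total would be 60 + 56 + 28 = 144, which does not match. For payment, at least, the assessments and the HbA1c reports are distinct items.

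**Step 2. Set the call rule against the schedule (Table 1 and the Primary Outcome section).**

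| HbA1c due | Linked questionnaire assessment | Is the HbA1c date an assessment named in the call rule? |
|---|---|---|
| Week 12 | Week 10 (postintervention) | No |
| Week 24 | Week 21 (3 months) | No |
| Week 36 | Week 33 (6 months) | No |
| Week 57 | Week 57 (12 months) | Yes |

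Table 1 shows no HbA1c at weeks 10, 21 and 33, and nothing except HbA1c at weeks 12, 24 and 36. The call rule therefore clearly reaches 1 of 4 HbA1c readings and 4 of 4 questionnaire assessments.

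**Step 3. Does another contact close the gap?**

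- The e-mail reminder applies to all four readings, so HbA1c is chased, but not by phone at weeks 12, 24 and 36.
- The non-use call may reach some of the same people. After week 8, however, use of the platform is left to the participant, and someone who is active but has not sent an HbA1c does not trigger it.
- The e-mails described in Procedures announce the 3-, 6- and 12-month assessments. The article does not mention a notice of the readings at weeks 12, 24 and 36.

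**Step 4. Can the loss be sized?** That needs the proportion of questionnaire completers who fail to report the following HbA1c. The article gives neither this nor any HbA1c reporting rate. The only response figure, 56% to 72%, is for an 8-week posttest in earlier trials on the platform. No size can be derived.

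**The case against.** The best defence is that the gap is one of wording. The article nowhere says that a missing HbA1c will not be followed by phone, and it condenses a full protocol that may settle the matter. Its labels are also loose. The Analysis Plan lists the assessment times for primary and secondary outcomes together as baseline, postintervention and 3, 6 and 12 months; the study objectives do the same for the follow-ups; and the HbA1c reports are themselves called assessments. On that usage, the week-12, 24 and 36 readings could belong to the assessments named in the call rule. There are other safeguards too: e-mail reminders, stated willingness to provide HbA1c as an entry condition, payment for each reading, the non-use call, and the call at week 57.

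Part of this stands. The intention is uncertain, and HbA1c is not left unchased. But the article does not leave the call rule to another document. It states the rule and names the triggers, in the same section that has just separated HbA1c from the postintervention assessment. Table 1 and the payment total both treat the HbA1c reports as separate items. On the more natural reading, three of the four readings lie outside the rule.

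**Conclusion.** The point holds as a cheap improvement to a stated rule. Only the week-57 HbA1c clearly falls under the reminder call; weeks 12, 24 and 36 have e-mail reminders and no call tied to a missing value. This rests on reading the assessments in the call rule as the questionnaire visits. The consequence is a risk of avoidable missing primary-outcome data, of unknown size.

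A reader might infer more, and the documents do not support it:

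- **That HbA1c will have more missing data than the questionnaires, or that bias will follow.** No HbA1c reporting rate is given, so neither can be shown.
- **That the 56% to 72% response rate measures the loss.** Those rates imply 400 × 0.28 = 112 to 400 × 0.44 = 176 questionnaire non-responders. These are the people the rule does phone. The exposed group is those who complete the questionnaire and then omit the HbA1c, and it has no figure.
- **That HbA1c has the weakest follow-up of all measures.** Daily items also have no call for a missed entry, although they have push notifications.
- **That US $5 against US $15 is a fault in the payment scheme.** The larger sum buys a battery of questionnaires, and the article does not say what the test costs the participant. Moving money to HbA1c would weaken the questionnaire incentive.

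**What to change.** In Procedures, extend the reminder call to any HbA1c report due at week 12, 24 or 36 that has not been received, on the same terms as the listed assessments and identically in both arms. Use the week-10, 21 and 33 contacts to announce the coming reading, so that participants have time to obtain a result. If staff already intend to make these calls, only the wording needs to change.

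The cost is one or two sentences in the protocol and one call per missed reading, so at most three extra calls per non-reporter, made by staff who already place reminder calls. Payments, visit dates and the analysis are unaffected.
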